### 2.7 Subject withdrawal

A subject must be withdrawn from the study if he/she withdraws consent. Subjects who 1) experience adverse events, or 2) have pre-existing violation of entry criteria may remain in the study unless the investigator determines that it is not in the subject’s best interest to continue. The specific reason for withdrawal should be indicated.

Subjects who have withdrawn from the study will be invited to follow up at the last study visit, i.e., week 16 after the randomization visit to detect any delayed clinical events.

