## 3 Study outcomes

### 3.1 Primary outcomes

1. The change in the TNSS at week 8.

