## 5 Sample size and statistical methods

### 5.1 Sample size calculation

This study is mainly focused on determining the efficacy of “Yupingfeng Powder with variation” for AR patients. The primary outcome is the TNSS. With reference to data from a previous similar study (Chen, 2015), the sample size was calculated using two means with software G*Power. The mean of nasal score of the treatment group was 0.5 ± 0.1 and that of the control group was 3.6 ± 0.2. To obtain a significance level of 5%, a power of 80%, 52 subjects are required. Allowing for a 10% dropout rate, 58 subjects are needed, with 29 in each group.

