### 5.2 Statistical analysis

Baseline data (gender, age, vital signs) will be descriptively summarized. Differences of measurement data between the groups will be assessed using *t*-test for normally distributed continuous variables and Wilcoxon signed rank test for non-normally distributed variables.

Measurement data of different groups in each visit will be reported as mean ± standard deviation (SD). Intra-group comparisons between baseline and each visit will be conducted by using paired *t*-test (or Wilcoxon signed rank test). Comparisons between groups will be conducted by using an analysis of variance (ANOVA), with other confounding factors like multicenter character conducting the covariate analysis. Statistical analysis for the data which do not meet above conditions (e.g., non-normal) will be conducted with the use of non-parametric test.

For AEs analysis, comparisons of the incidence rate of AEs between groups will be conducted with the use of χ^2^ test. The investigators need to list and describe the AEs occurred in this trial. If the data do not conform to χ^2^ test (data include 0, or theoretical frequency is below 5), Fisher’s exact test will be used.

For laboratory parameters, Spearman’s coefficient correlation will be used for comparison with different parameters and one way ANOVA test for significant correlation between groups.

All *p* values and 95% confidence intervals are two-sided, and *p* < 0.05 is considered statistically significant. Statistical analyses will be carried out exclusively by an independent statistician. All analyses will be performed by using SPSS, version 24 (SPSS).

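### The named ANOVA of week-8 TNSS change, unless combined with imputation, uses only subjects with a week-8 score, leaves early leavers' week-4 scores unused and does not name baseline TNSS as a covariate

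*Protocol article*

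**What the plan says.** The primary outcome is tied to one visit: "The change in the TNSS at week 8" (section 3.1). TNSS at weeks 4, 12 and 16 is secondary (section 3.2). Table 1 schedules TNSS at baseline and at weeks 4, 8, 12 and 16.

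For between-group differences, section 5.2 first names a t-test or a rank test for measurement data, and then states: "Comparisons between groups will be conducted by using an analysis of variance (ANOVA"), with covariate analysis for confounders of which centre is the only example. No repeated-measures or mixed model is named, and baseline TNSS is not mentioned as a covariate. Two neighbouring sentences are explicitly by visit, but they concern other things: "Measurement data of different groups in each visit will be reported as mean ± standard deviation (SD") is descriptive, and "Intra-group comparisons between baseline and each visit will be conducted by using paired" t-tests is within-group.

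On losses, section 5.1 says "Allowing for a 10% dropout rate, 58 subjects are needed, with 29 in each group". Section 2.7 invites withdrawn subjects back for the final visit at week 16 only. The article does not describe analysis sets or the handling of missing values.

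**The concern.** A t-test or ANOVA of week-8 change needs a week-8 value. A subject who attends week 4 and then leaves has a baseline and a post-treatment score on the primary scale, but contributes nothing to that test unless the missing value is imputed. The week-16 invitation does not supply a week-8 value.

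This could matter here because leaving may be related to symptoms. Section 2.3.2 bars steroids and antihistamines, which the introduction calls the mainstay treatments, and the comparator is a starch placebo. A subject whose symptoms persist has a plausible reason to leave. That is a mechanism, not a documented rate. If it operates unequally, the primary result compares selected subjects: losing non-improvers on placebo understates an effect, and losing them on the herbal arm overstates it.

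**Working it through.** **1. How many subjects.** From section 5.1: 52 evaluable and 10% dropout. 52 / 0.9 = 57.8, so 58 randomised, as stated. 58 × 0.9 = 52.2, so about 6 subjects lost. This is overall dropout in a 16-week study. Six is therefore the number without a week-8 score only if all of the planned dropout falls by week 8.

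**2. Direction, in a deliberately extreme case.** Suppose the worst share q of a normal outcome leaves an arm. The mean of those who stay shifts by −φ(z)/(1 − q) SD, where z is the (1 − q) quantile. This gives 0.109 for q = 5%, 0.195 for 10%, 0.274 for 15% and 0.350 for 20%. The bias in the benefit (control minus treatment) is then:

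| Loss, treatment / control | Bias (SD) |
|---|---|
| 10% / 10% | 0.195 − 0.195 = 0.00 |
| 15% / 5% | 0.274 − 0.109 = +0.17 |
| 5% / 15% | −0.17 |
| 20% / 0% | +0.35 |
| 0% / 20% | −0.35 |

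Equal loss of non-improvers gives no bias when there is no treatment effect. The sign otherwise depends on which arm loses more.

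**3. Size, by simulation.** None of these inputs is in the article. All are assumptions: 29 per arm; TNSS SD 2.5; true difference 1.2 at week 4 and 2.0 at week 8; 10% overall dropout after week 4, with logistic dependence on change at week 4. Correlations are 0.5 (baseline to week 4), 0.7 (week 4 to week 8) and 0.4 (baseline to week 8), or 0.6 throughout.

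| Correlations | Slope per TNSS point | Who leaves | Estimate from change-score ANOVA | Shortfall from 2.0 |
|---|---|---|---|---|
| 0.5/0.7/0.4 | about 1 | both arms | 1.83 | 0.17 / 2.0 = 8.5% |
| 0.5/0.7/0.4 | about 1 | placebo only | 1.44 | 0.56 / 2.0 = 28% |
| 0.6 throughout | about 1 | both arms | 1.91 | 0.09 / 2.0 = 4.5% |
| 0.6 throughout | about 1 | placebo only | 1.70 | 0.30 / 2.0 = 15% |
| 0.5/0.7/0.4 | 0.3 | both arms | 1.97 | 0.03 / 2.0 = 1.5% |
| 0.5/0.7/0.4 | 0.3 | placebo only | 1.73 | 0.27 / 2.0 = 13.5% |

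Repeat runs agreed to within about 0.03. Placebo-only loss means about 20% of that arm and none of the other. By symmetry, the same loss confined to the herbal arm would overstate the effect by as much: 2.0 + 0.56 = 2.56 in the second row. A likelihood estimate that also uses the week-4 scores returns 2.0 in the scenarios above.

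**4. What baseline adjustment does alone.** In a run with correlations 0.5/0.7/0.4 and slope 1, change-score ANOVA gave 1.81 (power 70%) with loss in both arms and 1.42 (47%) with placebo-only loss. Completers' ANCOVA on baseline TNSS gave 1.88 (85%) and 1.64 (72%). Adjustment therefore recovers much of the power and part of the bias. Even with uninformative dropout, the baseline-adjusted likelihood estimate had an SD about 10% to 18% smaller than change-score ANOVA.

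**5. Limit of the remedy.** If leaving is decided by the week-8 state itself, with one cut-off for both arms, 10% lost overall and an assumed true effect of 0.8 SD, losses are about 4% on treatment and 16% on control. The observed effect falls to 0.59 SD, a shortfall of 0.21 / 0.8 = 26%. This lies outside the range in step 3, and a model based on observed scores would not fully repair it.

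**The case against.** A reader might infer that section 5.2 prescribes a separate ANOVA at each visit and that every subject without a week-8 score is excluded. The text supports neither as a statement of fact. The by-visit wording belongs to the summaries and the within-group tests. A repeated-measures ANOVA is not ruled out, although its usual form also drops incomplete cases. ANOVA is compatible with multiple imputation that uses week 4, and a condensed article commonly leaves imputation and analysis sets to the full protocol or analysis plan, so silence on them is not an error.

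The size is also open to challenge. The 10% may fall partly after week 8. Section 2.7 keeps many subjects in: those with adverse events, or who "have pre-existing violation of entry criteria may remain in the study unless the investigator determines" otherwise. Every simulation input is assumed, the strength of the dropout dependence drives the result, and part of the low power comes from not adjusting for baseline rather than from missing data.

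These objections limit the wording and the magnitude. What stands is that the article does name a method for the between-group comparison, and that this method makes poorer use of the scheduled TNSS data than a readily available alternative.

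**Conclusion.** The point holds in a limited form. The named test, absent imputation, rests on subjects with a week-8 TNSS, does not use the week-4 score of those who leave, and is not stated to adjust for baseline TNSS. At most about 6 of 58 subjects are involved under the planned dropout.

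Bias is possible, not established. It is zero if dropout is unrelated to symptoms. Under the step 3 assumptions, with leaving driven by week-4 change, attenuation is about 1% to 9% with losses in both arms. It reaches about 28% only with all loss on placebo and strong dependence on symptoms. Loss confined to the herbal arm would overstate the effect instead. The tempting conclusion that the result is biased whenever non-improvers leave does not follow, because direction and size depend on how the losses divide between the arms. The gain in precision from baseline adjustment does not depend on any of this.

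**What to change.** In section 5.2, make the primary analysis one mixed model for repeated measures. It should include all randomised subjects in their allocated arm and TNSS at weeks 4, 8, 12 and 16, with arm, visit, arm-by-visit interaction and baseline TNSS as terms and an unstructured covariance. Report the week-8 arm contrast with its 95% confidence interval as the primary result, take the other visits from the same model, and keep the ANOVA as a supportive analysis.

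This costs wording only: no new data, visits or subjects. It should be settled before unblinding; section 9 reports 11 subjects recruited by 18 July 2022. The model is slightly more complex and assumes that dropout depends on observed scores, a weaker assumption than a completers' comparison makes. It cannot recover information from subjects with no TNSS after baseline.

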### 3.3 Study assessment

#### 3.3.1 Nasal symptom score

The TNSS will be self-assessed by subjects to evaluate four nasal symptoms (rhinorrhea, sneezing, nasal obstruction, and nasal itching), using a four-point scale as shown (Pfaar et al., 2014):
0=no symptoms

$$1=mild\;symptoms\;\left(sign/symptom\;clearly\;present,\;but\;minimal\;awareness;\;easily\;tolerated\right)$$

$$2=moderate\;symptoms\;\left(definite\;awareness\;of\;sign/symptom\;that\;is\;bothersome\;but\;tolerable\right)$$

$$3=severe\;symptoms\;\left(sign/symptom\;that\;is\;hard\;to\;tolerate;\;causes\;interference\;with\;activities\;of\;daily\;living\;and/or\;sleeping\right)$$

The higher the score, the more severity of the symptom.

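### Section 5.2 lets the observed distribution decide the primary TNSS test, so the test, effect estimate and covariate adjustment are not fixed in advance

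*Protocol article*

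**What the plan says.** Section 3.1 names one primary outcome: "The change in the TNSS at week 8". Section 3.3.1 describes the score: "The TNSS will be self-assessed by subjects to evaluate four nasal symptoms (rhinorrhea, sneezing, nasal obstruction, and nasal itching), using a four-point scale". Each item runs from 0 to 3, so the total is, by inference, an integer from 0 to 12.

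Section 5.2 has no separate paragraph for the primary outcome. For measurement data in general it states:

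- A t-test between groups if the variable is normal, otherwise a "Wilcoxon signed rank test for non-normally distributed variables".
- In the next paragraph: "Comparisons between groups will be conducted by using an analysis of variance (ANOVA), with other confounding factors like multicenter character conducting the covariate analysis".
- Then the switch: "Statistical analysis for the data which do not meet above conditions (e.g., non-normal) will be conducted with the use of non-parametric test".

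The section does not say which quantity is checked for normality (week-8 score, change or model residual), by what test or against what threshold. Covariates appear only in the ANOVA sentence, and baseline TNSS is not named among them. A later sentence says that "values and 95% confidence intervals are two-sided", without tying an interval to any branch.

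**The concern.** A confirmatory trial should have one primary test, one effect estimate and one adjustment set, all chosen before the outcome data are seen. Here the data choose. A bounded integer score with a floor at 0 can fail a normality check through granularity and flooring alone, so the non-parametric branch is a realistic destination.

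If the switch fires, the text no longer provides for covariate adjustment or a between-arm estimate. The sample size in section 5.1 rests on comparing two means, so the primary test could also differ from the comparison the trial was sized for. Because the trigger is undefined, two careful analysts could follow the same text to different primary p values.

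**Working it through.** **Inputs from the article.** Two-sided 5% level (5.2). Evaluable sample (5.1): "To obtain a significance level of 5%, a power of 80%, 52 subjects are required", and allocation is 1:1 (2.5), so 52 / 2 = 26 per arm. Section 5.2 gives no operating figure for the switch, so there is none to reproduce.

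**Why the SD is assumed.** Section 5.1 says: "The mean of nasal score of the treatment group was 0.5 ± 0.1 and that of the control group was 3.6 ± 0.2". The difference is 3.6 − 0.5 = 3.1 and the pooled SD is √[(0.1² + 0.2²)/2] = 0.158, a standardised difference of 3.1 / 0.158 = 19.6. At that size, 2 per arm already give power above 99.99%, so these inputs do not lead to 52 and cannot serve as a patient-level SD. That is a separate matter; only the 26 per arm is used here.

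**Assumptions.** Integer TNSS 0–12, baseline mean 6.5, week-8 control mean 4 (or 2), SD 2.5, correlation 0.5, effect 1.5 points, all set before rounding and clipping at the scale limits. The floor shrinks the observed effect, more so at control mean 2. Normality check: Shapiro-Wilk at 5% in either arm. Runs: 4,000–6,000 trials per scenario.

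**1. How often the switch fires.** Checked on change scores: 23–24% of trials. Checked on week-8 scores: 30% (control mean 4) to 99% (control mean 2) under no effect, and 74–100% with the effect. The unstated choice of what to check can decide the branch.

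**2. Type I error**

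| Procedure | Type I error |
|---|---|
| t-test on change | 4.9–5.1% |
| Rank test (Mann-Whitney) on change | 4.6–4.8% |
| Switch followed mechanically | 5.0–5.2% |
| Baseline-adjusted linear model | 4.8–5.1% |
| Better of t and rank, both on change | 5.6–5.7% |
| Better of t on change and ANOVA of week-8 values | 9.1–9.7% |
| Best of all three | 9.6–10.0% |

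A separate simulation (20,000 runs; normal, TNSS-like and strongly skewed data) gave 4.7–5.3% for the mechanical switch and 6.0–6.4% for a free choice between t and rank. The two tests disagreed on significance in 1.7–7.3% of runs.

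**3. Power at 1.5 points**

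| Procedure | Control mean 4 | Control mean 2 |
|---|---|---|
| t-test on change, always | 50.0% | 34.5% |
| Switch followed mechanically | 49.4% | 34.2% |
| Baseline-adjusted linear model | 65% | 59% |

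Cost of the switch: 50.0 − 49.4 = 0.6 points and 34.5 − 34.2 = 0.3 points.

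**4. Where the larger gain comes from.** Ignoring the floor, the SD of change is 2.5 × √[2(1 − 0.5)] = 2.5, and the residual SD after baseline adjustment is 2.5 × √(1 − 0.5²) = 2.17. The variance ratio is (1 + 0.5)/2 = 0.75, whichever test would otherwise be used. The gain therefore belongs to baseline adjustment.

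**The case against.** The strongest reply is that the rule is a common convention and does almost no harm when followed. That stands: type I error is about 5% and the power cost is under 1 point. With strongly skewed data and a shift of 2 points, the rank test did better than the t-test (96.7% against 89.7% power).

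Other replies hold in part:

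- *The t-test sentence follows one on baseline data and may concern baseline only.* That would remove one route. The ANOVA and the switch in the next paragraph would remain. With two arms, an unadjusted ANOVA on the same variable is the t-test in any case.
- *An article leaves detail to the SAP.* True of the normality check, its threshold and the covariate list. But the article itself commits to a data-triggered switch, and an SAP could undo that only by departing from this text.
- *Blinding and an independent statistician limit opportunism.* They do, but neither says which test is primary.

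Three stronger readings are tempting, and the documents do not support them:

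- *The switch nearly doubles the type I error.* The 9.6–10% arises mainly from also allowing an ANOVA of week-8 values: 9.1–9.7% remains with no rank test at all. Section 3.1 defines the outcome as a change, and nothing says the primary test uses raw week-8 scores.
- *The switch throws away 15 or more points of power.* That comparison is with a baseline-adjusted model, and 5.2 does not name baseline TNSS as a covariate. The plan cannot lose what it does not clearly contain.
- *The result may come with no estimate at all.* Section 5.2 has group means and SDs reported at each visit regardless of normality. What is missing is a stated between-arm estimate and interval for the non-parametric branch. That branch is silent on adjustment; it does not rule it out.

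**Conclusion.** The point holds as one of prespecification. Section 5.2 leaves the primary comparison of week-8 TNSS change to a t-test, an ANOVA with open-ended covariates or an unnamed non-parametric test, according to the observed distribution. The last branch has no stated adjustment or between-arm estimate.

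The measurable harm is small: none to type I error if the rule is followed mechanically, under 1 point of power in the TNSS-like scenarios, and about 5.6–6.4% type I error if the analyst may choose freely between t and rank on change. These figures rest on the assumed distributions, 26 per arm and a Shapiro-Wilk trigger, none of which 5.2 specifies.

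The linear model holds its level at this sample size without normality, so the switch protects nothing that needs protecting. Naming the signed rank test, a paired test, for a between-group comparison is a separate matter: correcting it would leave the switch in place.

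**What to change.** In section 5.2:

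1. State that week-8 TNSS change is analysed by one linear model (ANCOVA) with treatment and baseline TNSS, plus centre if there is more than one, whatever a normality check shows.
2. Report the adjusted mean difference with a two-sided 95% CI, using robust or bootstrap standard errors if residuals are skewed.
3. Delete the normality-triggered switch for the TNSS outcomes.
4. Keep an independent-samples rank test, named as such, as a sensitivity analysis only. This also covers the strongly skewed case in which a rank test has more power.

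The cost is wording only. Baseline TNSS is already collected at day 0 (Table 1), and no visit, sample or assessment changes. Section 9 reports 11 participants recruited by 18 July 2022. The change should be dated and made before unblinding, and any SAP should carry the same text.

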### 2.5 Randomization and blinding

The eligible subjects will be randomly assigned to either experimental group or control group at the ratio of 1:1. A randomization schedule will be generated by computer to assign subjects to the treatment sequences. Concealment of allocation will be ascertained by an independent research staff, and identically designed treatment packs will be used for study drugs.

This is a double-blind randomized controlled trial. All study investigators and subjects will be blinded in the study. The random allocations will be put into opaque envelops with sequential study numbers. Two sets of the envelope will be prepared, with one set for randomization at the site, and another set for storage in the investigator’s office for emergency un-blinding.

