### 2.6 Assessments

The changes of TNSS, RQLQ score for aged 13 and above and PADQLQ score for aged 5–12 and frequency and severity of AR episodes (VAS) will be evaluated at each study visit. Also vital sign and concomitant medications will be assessed and recorded. Subjects’ self-reported Chinese medicine adherence will be assessed, and reasons for skipping doses will be recorded.

Blood samples for serum cytokines (IL-10 and IL-17) will be collected at baseline, weeks 8 (±4 days) and 12 (±4 days). Stool specimen (within 24 h of the study visit day) will be collected at baseline and week 8 (±4 days). Subjects’ information will be kept anonymous.

Assessment of safety will be conducted by laboratory parameters and subjects’ reported adverse events and/or serious adverse events. The assessment of adverse event will be recorded according to CTCAE 4.0 which is a standard assessment tool. A direct telephone line will be provided so that subjects can report any adverse events during office hours between scheduled visits. The subjects will be recommended to attend Emergency Department at the nearest hospital beyond office hours if deemed necessary.

All subjects will be required to keep daily record for monitoring their compliance and side effects of the study treatment. Besides, they need to record 3 days of food diary before the day for taking stool specimens for gut microbiome analysis as the food intake may affect the gut species and influence the gut microbiome analysis result.

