### 3.2 Secondary outcomes

1. The change in the TNSS at weeks 4, 12, and 16.2. The changes in frequency of AR episodes and their severity VAS at weeks 4, 8, 12, and 16;3. The changes in the RQLQ score or PADQLQ score;4. The changes in the serum levels of total IgE and cytokines (IL-10 and IL-17) at weeks 8 and 12;5. The changes in the gut microbiota composition in stools at week 8; and6. Adverse events (graded by CTCAE) related to study treatment.

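### The laboratory analysis sentence gives Spearman's correlation and one-way ANOVA purposes they cannot serve, and leaves parameters, visits and baseline undefined

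*Protocol article*

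**What the plan says.** The protocol article, section 5.2, gives laboratory parameters a sentence of their own: Spearman's coefficient "will be used for comparison with different parameters and one way ANOVA test for significant correlation between groups".

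Other parts of the article bear on how to read it:

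- Section 2.5: two arms, with subjects "randomly assigned to either experimental group or control group at the ratio of 1:1".
- Section 2.6: "Assessment of safety will be conducted by laboratory parameters", together with the adverse events that subjects report.
- Section 3.2, fourth secondary outcome: "The changes in the serum levels of total IgE and cytokines (IL-10 and IL-17) at weeks 8 and 12".
- Table 1: the blood count and the renal and liver function tests stand under the laboratory heading, at screening and week 8. IgE (screening, weeks 8 and 12) and the two cytokines (day 0, weeks 8 and 12) stand under the outcome heading.
- Section 5.2, general rules: "Differences of measurement data between the groups will be assessed using" a t-test if normally distributed. Between-group comparisons use ANOVA with a covariate analysis for confounders such as centre, and data that do not meet the conditions go to an analysis that "will be conducted with the use of non-parametric test". All p "values and 95% confidence intervals are two-sided".

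**The concern.** Read literally, the sentence asks a correlation coefficient to make a comparison and asks an analysis of variance to test a correlation. Neither test can do the job given to it. An analyst following the text could report a table of correlations as the laboratory result, or describe a difference in means as a correlation.

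The sentence is also silent on three things needed to run an analysis: which parameters count as laboratory parameters, which visit is analysed, and whether the analysed quantity is the value at that visit or the change from the starting value. A one-way ANOVA has no covariate, so the rule as written makes no use of the screening or baseline measurement beyond what a change score would bring in, and it does not mention change.

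At stake is the laboratory half of the safety assessment. Table 1 provides only one on-treatment measurement of the blood count and organ function, at week 8. If the sentence is read widely, the fourth secondary outcome is at stake too.

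**Working it through.** The sentence states no figure, so there is none to reproduce. The check is whether each named test can detect what it is assigned to detect.

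**Inputs.** Two arms, 1:1 (section 2.5). Two-sided 5% level (section 5.2). 52 evaluable subjects (section 5.1), hence 52 / 2 = 26 per arm. The effect sizes are assumptions made for illustration, because the article gives none for laboratory data: an arm difference of 0.8 SD in one parameter, and a correlation of 0.5 between two parameters.

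**Step 1: what one-way ANOVA does with two arms.** With two groups, F = t², where t is the pooled two-sample statistic. On one simulated data set with 26 per arm, t² = 11.918 and F = 11.918, with p = 0.00114 for both. A one-way ANOVA by arm is therefore the ordinary two-sample comparison of means.

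**Step 2: what each test detects.** Simulation of 4,000 trials with 26 per arm and two normally distributed parameters. ANOVA compares the arms on the first parameter; Spearman relates the two parameters over all subjects. Share of runs with p < 0.05:

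| Truth | ANOVA by arm | Spearman between parameters |
|---|---|---|
| No arm difference, no correlation | 5.4% | 5.1% |
| Arm difference 0.8 SD, no correlation | 80.4% | 5.0% |
| No arm difference, correlation 0.5 | 4.3% | 94.9% |

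Spearman stays at its null rate when the arms differ, and ANOVA stays at its null rate when the parameters are correlated. The high rates depend on the assumed effects. The null rates do not, because they follow from what each test measures.

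**Step 3: scope.** Section 2.6 uses the term for safety, and Table 1 separates the safety tests from IgE and the cytokines. The narrower reading is therefore the more natural one: blood count, renal and liver function, screening to week 8. Section 5.2 does not say so. On the wider reading the sentence would also govern 3 markers × 2 visits = 6 between-arm comparisons.

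**Step 4: baseline.** A starting value exists for every parameter concerned: screening for the blood count, organ function and IgE, and day 0 for the cytokines. Section 2.4.1 allows the screening assessment to serve as baseline. Section 3.2 defines the marker outcomes as changes. No such definition is given for the safety tests.

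**The case against.** The strongest defence is that this is a slip of wording. Spearman is a legitimate tool for relating laboratory parameters to one another, and the word correlation in the second half can be read as a slip for difference, since ANOVA between two groups has no other use. On that reading the sentence contains a valid test. The general rules in section 5.2 would in any case give IgE and the cytokines a between-group ANOVA with a non-parametric fallback, and adverse events have their own chi-squared or Fisher comparison. A journal article may also leave transformations and covariates to an analysis plan that is not shown.

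Much of this stands. A reader might infer that the plan contains no valid between-arm comparison of laboratory data. The article does not support that: step 1 shows that ANOVA by arm is a defined and valid test. A reader might also infer that the serum markers have no usable analysis, or that safety rests on this sentence alone. Neither follows, for the reasons just given. Omitting a log scale is not in itself an error.

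What does not stand is the idea that nothing needs changing. The sentence is a stated rule, not an omitted detail, and it yields a correct analysis only if the analyst replaces a key word. A specific rule for laboratory data would ordinarily take precedence over the general ones, and the two differ: the general rule allows covariates and a one-way ANOVA has none. The fallback for skewed data is also unclear. One sentence leaves the non-parametric test unnamed, and another names the Wilcoxon signed rank test, a paired test, for differences between independent arms.

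**Conclusion.** The concern holds as a wrongly stated rule of unclear scope. Section 5.2 attaches Spearman and one-way ANOVA to purposes that neither can serve, and does not fix the parameters, the visit or the use of baseline.

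The size is modest. The sentence touches the safety blood tests at week 8 and, only on the wider and less natural reading, six comparisons of secondary markers. No numerical bias can be calculated, because the article gives no laboratory figures. The primary TNSS analysis is untouched. That the sentence is mis-stated follows from the definitions of the two tests and needs no assumption; the simulation only illustrates it, under the assumed 0.8 SD difference and 0.5 correlation. It should be corrected before the data are unblinded, since otherwise the analyst must guess what was meant.

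**What to change.** Replace the sentence in section 5.2 with a rule that does the following:

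- Names the parameters and visits: blood count and renal and liver function at week 8; IgE, IL-10 and IL-17 at weeks 8 and 12.
- Compares the arms on each by ANCOVA, with treatment and the screening or baseline value as terms, and reports the between-arm difference with its 95% confidence interval.
- Uses a log scale, or a rank-sum test, where the distribution is skewed.
- Limits Spearman's coefficient to exploratory associations between parameters.

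A count per arm of subjects above twice the upper reference limit may be added, but only as a descriptive summary: section 2.2.2 uses that limit for eligibility and does not define it as a safety endpoint.

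The cost is a change of wording and a little analysis work. Every measurement is already in the Table 1 schedule, so no further visits, samples or subjects are needed.
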